**Fig. 1 Fig1:**
[figure not shown]
Study Design Schema for COG ALTE22C1. ^See Table 1 for list of measures

Part 1 is conducted remotely through REDCap® [16, 17] (with a paper alternative) and consists of a medical record release, medical condition survey (completed by parent proxy and verified by medical record review), and saliva sample. Part 1 also includes a neurocognitive battery completed by parent proxy and designed to evaluate executive function and self-regulation, social competence, problem behaviors, autism spectrum behavior, communication, adaptive behavior, and quality of life. The measures included and their target area of assessment are shown in Table 1 [18–23]. Part 2 is focused on in-person assessments and requires local COG site activation of this central-IRB-approved protocol. For Part 2, consent is obtained by COG site personnel. Resources are available to sites that support inclusion in research of persons with intellectual disabilities [24], including a visual break board for survivors to direct the pace of the consent conversation and request a pause or stop if needed (Fig. 2) [25]. Part 2 comprises an in-person, COG Long-Term Follow-Up Guidelines [26]-informed and Down Syndrome Guidelines [27, 28]-informed long-term follow-up visit. Results of the clinic visit, including diagnosis and treatment information, complete review of systems, vital signs and anthropometrics, Tanner staging, list of medication, and results of any laboratory or diagnostic tests, are reported by the COG site-based research team via REDCap® to the central data coordinating center. Part 3 comprises a comprehensive, in-person neurocognitive evaluation on a subset of ALL survivors and research blood draw, also requiring COG site activation in addition to COG site-based training. The COG site-based research team administers the NIH Toolbox Cognitive Battery (NIH-CB) using a study-supplied tablet. The NIH-CB is validated in persons with intellectual disability [29, 30] and includes seven tests: Flanker Inhibitory Control and Attention, Dimensional Card Sort, List Sorting Working Memory, Oral Reading Recognition, Pattern Comparison Processing Speed, Picture Sequence Memory, and Picture Vocabulary. The Part 3 required research blood draw is banked for future assessment of leukocyte telomere length by telomere flow-fluorescence in situ hybridization (FISH) [31].

**Table 1 Tab1:** Part 1 and Part 3 Neurocognitive Measures Included in COG ALTE22C1

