For Part 3, we will use Cox regression to estimate the HR and 95% CI for number, severity, and type of CHC, as well as for neurocognitive deficits dichotomized as clinically significant impairment yes/no (≤ 1.5 SD outside of the mean for the age-normative sample) according to age at diagnosis, years off therapy, sex, race/ethnicity, diagnosis, and treatment exposures. We will use Cox regression to estimate HR and 95% CI for number, severity, and type of CHC by number of birth defects, as well as explore the role of DS-ALL susceptibility variants identified in our genome-wide assessment [46] on DS-associated CHC in survivors. All models will be adjusted for sex, genetic ancestry (estimated using the top 10 principal components), and age at diagnosis (years). We will determine genetically-estimated telomere length (TL) using methods described previously [47] and use a multivariable Cox proportional hazard model to estimate HR, 95% CI for the association between each of nine variants and risk for neurocognitive deficit ≤ 1 SD below the mean, considering the weighted and unweighted risk score from the number of risk alleles present and previously-published beta estimates. For flow-FISH analyses, TL ≤ 1 st percentile is considered ‘very short,’ as previously defined [48]. We will determine ORs for neurocognitive deficits ≤ 1.5 SD below the mean for a DS age-normative sample in subjects with TL > or ≤ 1 st percentile, adjusted for relevant covariates and treatment factors (e.g. ALL, AML). We will report 95% CI, p values using McNemar’s test (two-tailed p-value of 0.05 statistically significant).

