### Study progress

ALTE22C1 opened for recruitment in June 2023. As of August 2025, 55 COG sites have activated the protocol and 112 participants have been enrolled to Part 1, 73 to Part 2, and 6 to Part 3.

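### McNemar's test is named for the telomere (flow-FISH) odds ratio, but the comparison is between unpaired subjects, so its p-value does not test that odds ratio

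*Protocol article*

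**What the plan says.** The Part 3 paragraph of Statistical analyses (Protocol article) sets out the flow-FISH telomere analysis.

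- Outcome: "We will determine ORs for neurocognitive deficits ≤ 1.5 SD below the mean for a DS age-normative sample".
- Comparison: the ORs are to be estimated "in subjects with TL > or ≤ 1 st percentile, adjusted for relevant covariates and treatment factors (e.g. ALL, AML").
- Exposure cut: telomere length at or below the 1st "percentile is considered ‘very short,’ as previously defined" in an outside source.
- Inference: 95% CIs and "p values using McNemar’s test (two-tailed p-value of 0.05 statistically significant").

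Other sections show who can enter this analysis.

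- Under Study design, "Part 3 comprises a comprehensive, in-person neurocognitive evaluation on a subset of ALL survivors and research blood draw", so the flow-FISH sample comes from ALL survivors.
- Under Data collection, DS controls neither take the NIH Toolbox nor give a specimen.
- Under Recruitment, population, and eligibility, controls are frequency-matched to cases rather than matched in individual pairs.
- Under Aims, the molecular correlations, including telomere length, are exploratory.
- Under Study progress, "112 participants have been enrolled to Part 1, 73 to Part 2, and 6 to Part 3".

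**The concern.** Each subject contributes one telomere category and one deficit status, and the OR compares deficit between two separate sets of people. McNemar's test is built for two binary readings on the same unit or matched pair. Run on a table of very short telomeres by deficit, it treats those two variables as the pair and compares their marginal frequencies. That is a different null hypothesis from OR = 1. It also has no place for covariates, so it cannot supply the p-value for an adjusted OR.

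The telomere result could therefore be called significant when deficit and telomere length are unrelated, or non-significant when they are strongly related. The printed p-value could contradict the OR beside it. This is not a detail left to an analysis plan: the article itself names the test, its sidedness and its significance level.

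**Working it through.** The article gives no sample size, power, expected number exposed or effect size for this analysis, so there is no planned figure to reproduce. The check is whether the named test answers the stated question.

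**1. Is anything paired?** A case-control pair is impossible, because DS controls give no specimen. Matching elsewhere is by frequency. No repeated measurement is described for this analysis. The groups are independent.

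**2. What McNemar's test does here.** Cross-classify N subjects:

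| | Deficit | No deficit |
|---|---|---|
| Very short | a | b |
| Not very short | c | d |

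- The OR is ad/(bc).
- McNemar's test uses only b and c. Exactly, p = 2 × P(X ≤ min(b, c)) with X ~ Binomial(b + c, 0.5), capped at 1.
- Its null is b = c in expectation. That is the same as (a + b)/N = (a + c)/N: the share very short equals the share with a deficit.
- The OR that belongs to this test is b/c, not ad/(bc).

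**3. Two illustrative tables, N = 200.**

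| a, b / c, d | Share very short | Share with deficit | OR = ad/(bc) | b/c | McNemar p | Fisher p |
|---|---|---|---|---|---|---|
| 4, 36 / 16, 144 | 40/200 = 20% | 20/200 = 10% | (4 × 144)/(36 × 16) = 1 | 36/16 = 2.25 | 0.008 | 1.0 |
| 10, 10 / 10, 170 | 20/200 = 10% | 20/200 = 10% | (10 × 170)/(10 × 10) = 17 | 10/10 = 1 | 1.0 | 9e-7 |

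The first table has no association and is declared significant. The second has a strong association and is missed.

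**4. Rejection rate with no association (exact McNemar, two-sided 0.05).** The inputs are assumptions, because the article gives neither the Part 3 target nor either prevalence. The 6.7% is Φ(−1.5), the deficit rate if survivors match a normal DS norm. The other prevalences are for illustration.

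| Very short | Deficit | N = 50 | N = 100 | N = 200 |
|---|---|---|---|---|
| 1% | 6.7% | 8% | 41% | 83% |
| 5% | 6.7% | 2% | 4% | 7% |
| 10% | 20% | 20% | 42% | 77% |
| 1% | 30% | 99% | 100% | 100% |

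At N = 30 with 1% very short and 6.7% deficit, the rate is 1%. Fisher's exact test, simulated with no association at N = 50, 100 and 200 (1%, 5% or 10% very short; 6.7%, 20% or 30% deficit), rejected between 0.1% and 3.6% of the time, so it keeps the 5% level.

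**5. Number with very short telomeres.** The expected number is n × p, and both are unknown.

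- At p = 1%: 6 × 0.01 = 0.06; 50 × 0.01 = 0.5; 200 × 0.01 = 2.
- At n = 200 with p = 5% to 20%: 10 to 40.

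The 200 is the DS-ALL sample in the power section for the chronic-condition comparison. It is not a Part 3 target.

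**The case against.** The best defence is that the sentence is a slip of wording. An adjusted OR implies a regression model, and that model supplies its own CI and p-value. The aim is exploratory, the blood is banked for later assay, and no primary or secondary result depends on this line. All of that stands and lowers the weight. It does not make the test right: the article names McNemar's test, and an analyst following the text would use it.

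Three stronger readings are tempting but are not supported.

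- *Only about two subjects will be exposed, so the OR cannot be estimated.* This needs all 200 DS-ALL survivors in Part 3 and a 1% prevalence. Part 3 is a subset of unstated size, the cut comes from an outside source, and survivors need not follow its reference distribution. Sparse cells are possible but not shown. The mismatch between test and OR holds at any number exposed.
- *A false positive is nearly certain.* That holds only when the two prevalences are far apart and N is large enough. With 5% very short and 6.7% deficit, the rate stays between 2% and 7% for N from 50 to 200.
- *The ALL/AML adjustment biases the result.* The adjustment examples do name it ("percentile, adjusted for relevant covariates and treatment factors (e.g. ALL, AML"), and it is constant when only ALL survivors enter. A constant covariate drops out of the model and biases nothing.

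**Conclusion.** The point holds, at moderate severity. As written, the CI and p-value for an adjusted OR between independent subjects are to come from a paired, unadjusted test of a different hypothesis. This follows from the text alone and needs no assumption about sample size or prevalence.

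The numerical consequence does need such assumptions. With no association, the rejection rate ranges from near 0% to 100%, and a strong association can be missed entirely. The article does not allow a single expected error rate to be stated. The sentence might also be read as applying McNemar's test to the p-value only, with the CI taken from elsewhere. The p-value would still not belong to the OR.

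Naming ALL/AML among the adjustment factors is a minor inconsistency with the Part 3 population.

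**What to change.** Delete McNemar's test. State that the OR, its 95% CI and its p-value all come from the same logistic regression, with Firth penalisation or exact methods if cells are sparse. If an unadjusted comparison is reported, use Fisher's exact test.

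Remove ALL/AML from the adjustment examples for this analysis. State the expected Part 3 sample size and the expected number with very short telomeres, so that readers can judge the precision.

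An analysis of telomere length as a continuous variable could be added if few subjects fall below the cut. That is optional, because it changes the question asked.

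The cost is one or two sentences, with no change to data collection. Part 3 is still accruing and its blood is banked for later assay, so the change can be made before the analysis.

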### Study progress

ALTE22C1 opened for recruitment in June 2023. As of August 2025, 55 COG sites have activated the protocol and 112 participants have been enrolled to Part 1, 73 to Part 2, and 6 to Part 3.

## Discussion

ALTE22C1 is an ongoing multisite study open through the COG cooperative group that will compare the CHC and neurocognitive outcomes in DS-AL survivors, compared to persons with DS and no cancer history. The hybrid recruitment design leverages both COG patient registries as well as site-based recruitment of non-registry participants, thus supporting the collection of both patient-reported outcomes and data from in-person clinical assessment, in addition to reducing potential selection bias associated with exclusively registry-based recruitment. The steady pace of accrual since study launch suggests support from a motivated patient population as well as suggesting benefit to a study design that supports remote participation and that minimizes burden on participating COG sites.

There is a substantial dearth in our understanding of the long-term impact of cancer treatment in this vulnerable population. To date, the published data have compared late effect prevalence in this at-risk population to non-DS survivors of AL, which disregards the effect of the baseline excess risk for CHC experienced by individuals with DS. For example, the CCSS compared CHC in 154 DS-AL survivors to non-DS survivors matched by diagnosis, age at diagnosis, race/ethnicity, sex, radiation, and chemotherapy exposures, indicating that DS-AL survivors (median age 20 years, range 10–48 years) were at greater risk for serious CHC and ≥ 3 CHC than non-DS AL survivors, with a 25 year CHC cumulative incidence of 83% vs. 69% [49]. Similar results were seen in a smaller cohort of DS-AML survivors [50]. One study evaluated neurocognitive outcomes in DS-AL survivors vs. DS children without AL and found greater deficits in verbal intelligence, spelling, receptive and expressive vocabulary, visual-motor skills, and adaptive function [39]. In a more recent study that compared neurocognitive outcomes between 117 DS controls and 43 DS-AL survivors, differences were observed between the groups in completion rates for executive function and processing speed measures as well as in performance and rating measures of executive function [51].

By addressing this key knowledge gap, the results of ALTE22C1 are expected to inform clinical practice related to both upfront AL treatment and survivorship care. Indications of heightened risk for acute and late-onset chemotherapy-related toxicities specific to the DS population may lead to a change in approach for future clinical trials to mitigate risk for adverse outcomes. The current version of the COG Long-Term Follow-Up Guidelines for Survivors of Childhood, Adolescent, and Young Adult Cancers [52] does not include DS status when assessing treatment-related late effects risk. Robust evidence for excess risk from studies such is this will support added surveillance, leading to early detection, intervention, and a potential reduction in the outcome disparities experienced by this vulnerable population.

## Data Availability

No datasets were generated or analysed during the current study.

## Abbreviations

AL: Acute leukemia
ALL: Acute lymphoblastic leukemia
AML: Acute myeloid leukemia
CCSS: Childhood cancer survivor study
CHC: Chronic health conditions
CI: Confidence interval
COG: Children’s Oncology Group
CTCAE: Common Terminology Criteria for Adverse Events
DS: Down syndrome
LTS: Long-term survivor
ML-DS: Myeloid leukemia of Down syndrome
OR: Odds ratio
SD: Standard deviation
TL: Telomere length
